## Screening Visit (Day 0), Screening Visit can be done 21 day before planned visit.

1. Investigator will review all inclusion and exclusion criteria and determine subject's eligibility
2. Informed consent is signed
3. Demographics (date of birth, gender, ethnic origin)
4. Medical history (including concomitant medication use and medical conditions)
5. Complete physical examination including vital signs (blood pressure and heart rate), body weight (kg) and height (cm)
6. Chest X-ray (if not obtained within the past 6 months prior to study start), if an Chest X-ray was done within the past 6 month the film must be available for reading by the PI
7. Electrocardiogram (ECG)
8. Withdrawal of 22 mL venous blood for laboratory tests, which include,:
   1. Serum chemistries including electrolytes (K, Na, Cl, HCO3, Ca, and P), liver function tests (AST, ALT, LDH, AlkP, GGT, and Bilirubin), Renal function tests (BUN, and Creatinine,) CPK, Serum proteins(Albumin,Globulin), Cholesterol, and Uric Acid
   2. Complete blood cell count including white blood cells differential count (CBC), and coagulation profile (PT, PTT)
   3. ANF, ESR, C3
   4. Serology: HBsAg, HCV and HIV
   5. Serum pregnancy test
9. Subjects failing to meet the entry criteria will be consider screening failures. A screening log, containing the screening number, subject’s initials and reason(s) for failure, is to be maintained by the investigator in the study files.

## Baseline Visit (Visit 1-1a, Day 1-2, Treatment visit) Baseline Visit can be done ± 1 day from planned visit.

1. Baseline data will be collected at time 0 immediately prior to infusion of study medication and at 24h (baseline a) from initiation of infusion.
2. Body weight, vital signs and physical examination.
3. Concomitant medications
4. Electrocardiogram (ECG) (will be performed only at time 0 and 8hr post infusion.)
5. Withdrawal of 22 mL venous blood for laboratory tests, pre infusion (time 0) and 24h post infusion which include:
   1. Serum chemistries including electrolytes (K, Na, Cl, HCO3, Ca, and P), liver function tests (AST, ALT, LDH, AlkP, GGT, and Bilirubin), Renal function tests (BUN, and Creatinine,) CPK, Serum proteins(albumin and globulin), Cholesterol, and Uric Acid
   2. Complete blood cell count (CBC), and coagulation profile (PT, PTT)
   3. ANF, ESR, C3 (C3 test should be done both at time 0 and 24hr post infusion)
6. Urinalysis
7. 5mL PK blood for plasma sample prior to dosing
8. Prepare drug (vehicle) for infusion (see Section 6.5)
9. Administer the investigational drug (see Section 6.2) and monitor safety as described below:

| Parameters | Pre-infusion | During and Post-infusion |
| --- | --- | --- |
| Temperature | + | +a |
| Blood Pressure | + | +a |
| Pulse Rate | + | +a |
| Respiratory Rate | + | +a |

a Vital signs will be measured prior to infusion and every 30 minutes during infusion and at 8, 24 hours post infusion

1. Withdrawal of 5 ml blood for plasma samples at 0,80, 210 minutes and 24 hours post-infusion.
2. Withdrawal of 5ml blood for serum for antibody detection and characterization at 24h post infusion
3. Adverse events

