**Secondary**

To evaluate the pharmacokinetic profile of prGCD after IV administration in healthy volunteers

**Design:** This is a phase I, non-randomized, open label, safety study of three escalating single doses of human prGCD administered as an intravenous infusion (IV) in healthy volunteers.

Eligible subjects will receive the vehicle on Day 1 followed by human prGCD on Day 8 (15 units/kg), Day 15 (30 units/kg), and Day 22 (60 units/kg). At each visit, blood samples for clinical chemistries and CBC with a differential count, will be collected prior to dosing and at 24h post the initiation of the infusion. Blood samples for PK analysis will be collected at 0, 5, 45, 80, and 90 minutes during the infusion and 100, 115, 130, 150, 180, 210 minutes, and 24 hours post-infusion. Subjects will be discharged from the clinic after 8 hr on the day of the infusion and will arrive again 24 hr from the initiation time of infusion for blood draw and additional safety assessment.. A follow-up visit will occur on Day 29.

**Blinding:** Open-label study

**Sample Size:** A total of 6 healthy volunteers will participate

**Method of Subject Assignment:** Open label

**Primary Outcome Measures:** Safety as measured by adverse events, changes in vital signs, physical examination and laboratory test results.

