**Secondary Outcome Measures:**

- Pharmacokinetic parameters
- Immunological profile including: IgE, anti human prGCD antibodies, eosinophils and proteinuria

**Plan for Obtaining Adverse Events:** All volunteered, elicited and observed adverse events (AEs) will be documented.

**Plan for Data Analyses:** Safety parameters, as well as changes from baseline, will be examined and summarized for descriptive purposes. Safety will also be assessed through the recording of adverse events. Adverse events will be classified by body system using the MedDRA classification, and tabulated based on the incidence, severity, and causality to study treatment.

TABLE OF CONTENTS

[LIST OF ABBREVIATIONS 9](#__RefHeading___Toc102708696)

[1. INTRODUCTION 10](#__RefHeading___Toc102708697)

[1.1. Rationale 10](#__RefHeading___Toc102708698)

[1.2. Summary of non clinical and clinical studies 10](#__RefHeading___Toc102708699)

[2. OBJECTIVES 11](#__RefHeading___Toc102708700)

[2.1. Primary 11](#__RefHeading___Toc102708701)

[2.2. Secondary 11](#__RefHeading___Toc102708702)

[3. STUDY DESIGN 11](#__RefHeading___Toc102708703)

[3.1. Indication 12](#__RefHeading___Toc102708704)

[3.2. Blinding 12](#__RefHeading___Toc102708705)

[3.3. Controls 12](#__RefHeading___Toc102708706)

[3.4. Randomization 12](#__RefHeading___Toc102708707)

[3.5. Dose Rationale 12](#__RefHeading___Toc102708708)

[3.6. Stopping Criteria 13](#__RefHeading___Toc102708709)

[3.7. Study Flow Chart 13](#__RefHeading___Toc102708710)

[4. SUBJECT POPULATION 13](#__RefHeading___Toc102708711)

[4.1. Inclusion Criteria 13](#__RefHeading___Toc102708712)

[4.2. Exclusion Criteria 13](#__RefHeading___Toc102708713)

[5. STUDY PROCEDURES AND VISIT SCHEDULE 14](#__RefHeading___Toc102708714)

[5.1. Pre-Screening Visit (Day -1) 14](#__RefHeading___Toc102708715)

[5.2. Screening Visit (Day 0) 14](#__RefHeading___Toc102708716)

[5.3. Baseline Visit (Visit 1, Day 1, Treatment visit) Baseline Visit can be done ± 1 day from planned visit. 14](#__RefHeading___Toc102708717)

[5.4. Visits 2-2a, 3-3a and 4-4a (Treatment Visits, Day 8-9, Day 15-16, and Day 22-23), visit 2,3 and 4 can be done ± 1 day from planned visit. 15](#__RefHeading___Toc102708718)

[5.5. Visit 5 (Follow-up Visit, Day 29) 16](#__RefHeading___Toc102708719)

[5.6. Observations and Measurements 16](#__RefHeading___Toc102708720)

[5.6.1. Blood Tests. 16](#__RefHeading___Toc102708721)

[5.6.2. PK Analysis 16](#__RefHeading___Toc102708722)

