# STUDY DESIGN

The proposed investigation will be a phase I, single-center, non-randomized, open label, safety study of three single escalating doses of human prGCD administered as an intravenous infusion (IV) to six healthy volunteers. Subjects meeting the entry criteria will be eligible to receive study drug. Urine will be collected 24 hours prior to screening to assess renal function. Seven visits are scheduled for this study: pre-screening (Day -1), Screening (Day 0), baseline (Day 1), Visit 1 (Day 8), Visit 2 (Day 15), Visit 3 (Day 22) and follow-up visit (Day 29). The study procedures for each visit are presented in the study flow chart (Appendix 1). The duration of study is 29 days.

Subjects will be monitored over 24 hours from the commencement of the infusion of each dose at the Hadassah medical center, Phase I unit. The treatment will consist of a single dose infused for 1.5 hours (1.5mL/min). The infusion rate may be adjusted according to subject symptoms and signs: slower rate (1mL/min) upon adverse effect or faster (2mL/min.) upon lack of any symptom and signs. The vital signs for each subject will be monitored during infusion. ECG will be done at baseline and at 8 hours following the infusion. Subjects will remain at the clinic for 8 hours post-infusion and will be discharged if no AEs are observed. Subjects will return to the clinic 24h post initiation of infusion for additional safety assessment. Vital signs will be recorded during the infusion and PK sampling every 30 minutes (up to 3.5 hrs), and afterward at 8 and 24hrs post infusion.

Each subject will receive a single IV dose of vehicle at the baseline visit (Day 1). Blood samples for PK will be collected prior to dosing (0) and at 5, 45, 80 and 90 minutes during the infusion and 100, 115, 130, 150, 180, 210 minutes and 24 hours from initiation of infusion. On Day 8, subjects will receive a single 15 units/kg of study drug and will have the same blood samples taken as per Day 1. On Day 15, subjects will receive a single 30 units/kg of study drug and have the blood samples taken as per Day 1. On Day 22, subjects will be administered a single dose of study drug of 60 units/kg, and have the same procedures performed as Day 1.

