# APPENDIX 1: Study flow chart

|  | Pre-Screening | Screening | Visit 1-  (Baseline) | Visit 1a-  (Baseline a) | Visit 2 | Visit 2a | Visit 3 | Visit 3a | Visit 4 | Visit 4a | Follow-up visit |
| --- | --- | --- | --- | --- | --- | --- | --- | --- | --- | --- | --- |
| Day | -1 | 0 | 1 | 2 | 8 | 9 | 15 | 16 | 22 | 23 | 29 |
| Informed consent |  | x |  |  |  |  |  |  |  |  |  |
| Inclusion/exclusion criteria |  | x |  |  |  |  |  |  |  |  |  |
| Demographics |  | x |  |  |  |  |  |  |  |  |  |
| Medical history & current medications |  | x |  |  |  |  |  |  |  |  |  |
| Concomitant medications |  | x | x |  | x |  | x |  | x |  | x |
| Vital Signs |  | x | xb | x | xb | x | xb | x | xb | x | x |
| Temperature |  | x | x |  | x |  | x |  | x |  | x |
| Body Weight |  | x | x |  | x |  | x |  | x |  | x |
| Physical Examination |  | xd | x |  | x |  | x |  | x |  | x |
| Chest X-ray |  | xc |  |  |  |  |  |  |  |  |  |
| IV infusion |  |  | x |  | x |  | x |  | x |  |  |
| AE Assessments |  |  | x | x | x | x | x | x | x | x | x |
| ECG |  | x | x |  | x |  | x |  | x |  |  |
| Laboratory tests |  |  |  |  |  |  |  |  |  |  |  |
| Serum chemistriese |  | x | x | x | x | x | x | x | x | x | x |
| CBC PT, PTT, C3, ESR, ANFe |  | x | x | x | x | x | x | x | x | x | x |
| Urinalysis at 0 and 24 hours post infusion | xg | x | x | x | x | x | x | x | x | x | x |
| plasma prGCD protein level (PK)f |  |  | x | x | x | x | x | x | x | x | x |
| Eosinophils, IgE |  | x | x | x | x | x | x | x | x | x | x |
| Serum pregnancy test |  | x |  |  |  |  |  |  |  |  | x |
| Anti human prGCD antibodies in serum |  |  |  | x |  | x |  | x |  | x | x |
| HBsAg, HCV and HIV |  | x |  |  |  |  |  |  |  |  |  |

a Visit which is scheduled 24 h post each infusion visit

b Vital signs (temperature, blood pressure, pulse rate, respiratory rate and cardiac rhythm) will be measured prior to infusion and every 30 minutes during infusion and at 8 and 24 hours post infusion

c If not obtained within the past 6 months prior to study start and available for reading by the PI

d Including height

e Withdraw 22 ml whole blood pre infusion (time 0) and 24h post infusion

f Withdrawal of 7 ml blood at, 0 and at 5, 45,80 and 90 minutes during the infusion and 100, 115, 130, 150, 180, 210 minutes and 24 hours from infusion initiation

g Urine collection 24 hours prior to screening visit to assess renal function

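### Section 5.3 lists 4 vehicle-day PK draws where the rest of the protocol gives 12, and sections 5.2 and 5.3 omit IgE, so the IgE change across vehicle may go unmeasured; PK sample volume (5 or 7 mL) also conflicts

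*Protocol*

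**What the plan says.** **PK draws on the vehicle day.** Section 5.3 (Baseline Visit) lists "Withdrawal of 5 ml blood for plasma samples at 0,80, 210 minutes and 24 hours post-infusion". Section 3 says of the same day: "Blood samples for PK will be collected prior to dosing (0) and at 5, 45, 80 and 90 minutes during the infusion", followed by six further times to 210 minutes and one at 24 hours. It then defines Day 8 by reference to Day 1: subjects "will have the same blood samples taken as per Day 1". The synopsis, describing every visit, agrees with section 3: "Blood samples for PK analysis will be collected at 0, 5, 45, 80, and 90 minutes during the infusion", then the same later times.

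**PK volume.** Sections 5.3 and 5.4 specify 5 mL. Appendix 1, footnote f, reads "Withdrawal of 7 ml blood at, 0 and at 5, 45,80 and 90 minutes during the infusion" and continues to 24 hours. That footnote belongs to the plasma PK row, which is marked at all infusion visits.

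**IgE.** The synopsis lists as a secondary outcome "Immunological profile including: IgE, anti human prGCD antibodies, eosinophils and proteinuria". The Appendix 1 row "Eosinophils, IgE" is marked at Screening, Visit 1, Visit 1a and every later visit. The test lists in sections 5.2 and 5.3 end without IgE. In the visit-by-visit text it first appears in section 5.4 (Visit 2, Day 8).

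**Control.** The synopsis states that each subject acts as his or her own control through the vehicle infusion. There is no randomized or parallel control group, and six volunteers are planned.

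**The concern.** Section 5.3 is the procedure list that staff would naturally have in hand on the vehicle day, and it differs from the flow chart on what is collected. IgE matters most. It is a named outcome in a trial of an enzyme made in plant cells, and nothing else in the section 5.3 list supplies it. If the sample is not assayed before and after vehicle, a 24-hour IgE change after an active dose has no 24-hour change after vehicle beside it. An analysis plan cannot restore a measurement that was never made, and the protocol makes no provision for stored serum to be assayed later.

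The PK draw count is a second conflict on the same day. The volume conflict is separate and runs through all infusion visits. It leaves the total blood taken from each volunteer undefined.

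**Working it through.** **1. Vehicle-day PK draws, side by side**

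| Place | Times | Count | Volume |
| --- | --- | --- | --- |
| Synopsis | 0, 5, 45, 80, 90, 100, 115, 130, 150, 180, 210 min, 24 h | 12 | not given |
| Section 3 | same | 12 | not given |
| Section 5.3 | 0, 80, 210 min, 24 h | 4 | 5 mL |
| Appendix 1, footnote f | same as synopsis | 12 | 7 mL |

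The four times are a subset of the twelve. The eight absent from 5.3 are 5, 45, 90, 100, 115, 130, 150 and 180 minutes. Over six subjects this is 6 × 4 = 24 samples against 6 × 12 = 72. PK blood on that day is 4 × 5 = 20 mL, 12 × 5 = 60 mL or 12 × 7 = 84 mL per subject.

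Within section 3 the cross-reference to Day 1 resolves to twelve points. Only a reader who carried section 5.3's Day 1 into it would get four on the dose days, and section 5.4 lists twelve there.

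**2. What four points can still show**

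No prGCD is given on Day 1, so the samples serve as a background. For a constant level c, the trapezoidal area from 0 to 1440 minutes is 1440 × c on either grid. A flat background is therefore captured equally well. What is lost is a time-matched blank at the other eight times.

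**3. IgE values before the first active dose, per subject**

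- Appendix 1: Screening, Visit 1, Visit 1a, Visit 2 at time 0 = 4.
- Lists in 5.2 to 5.4: Visit 2 at time 0 only = 1. Section 5.4 draws its laboratory blood before infusion and at 24 h, so this value does precede prGCD.
- Pairs spanning the vehicle infusion (Visit 1 time 0 and Visit 1a): 1 by Appendix 1, 0 by section 5.3.

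**4. Other secondary measures if section 5.3 alone is followed**

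- Eosinophils: kept. The abbreviation list defines CBC as including the differential.
- Proteinuria: urinalysis is listed.
- Antibodies: serum at 24 h is listed, as in Appendix 1.
- IgE: not listed.

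**5. Total study blood per subject**

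Common inputs from section 5: laboratory draws of 22 mL at screening, twice at each of four infusions, and at follow-up, (1 + 8 + 1) × 22 = 220 mL; antibody serum, 5 × 5 = 25 mL. Sum 245 mL.

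- Section 5 as written: PK 4 × 5 + 3 × 12 × 5 + 5 (follow-up) = 205; total 205 + 245 = **450 mL**.
- Twelve points on all four days at 5 mL: PK 4 × 12 × 5 + 5 = 245; total **490 mL**. This is a mixed case, since section 3 states no volume.
- Appendix 1 at 7 mL: PK 4 × 12 × 7 + 7 = 343; total 343 + 245 = **588 mL**.

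The 138 mL range splits into 8 × 5 = 40 mL from the draw count and 49 × 2 = 98 mL from the volume. The 588 mL applies footnote f's volume to the follow-up sample as well; section 5.5 gives 5 mL there, which would make it 586 mL.

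Sections 5.3 and 5.4 also list a pre-dose PK draw on its own line (in 5.3, "5mL PK blood for plasma sample prior to dosing"). The totals treat it as the time-0 sample. If it were an additional draw, section 5 would rise by 4 × 5 = 20 mL to 470 mL.

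**The case against.** The strongest reply is that the flow chart governs. Section 3 says that the procedures for each visit are those in Appendix 1, section 3.7 points there too, and the chart marks IgE at all three places in question. The lists in 5.2 and 5.3 are introduced as what the tests include, so they need not be exhaustive. Section 5.6.1 names IgE among the study's blood tests without limiting it to particular visits. All of this stands, and it makes it quite possible that IgE would be assayed on the vehicle day. It does not remove the conflict: section 5.4 itemises IgE under a similar introduction and section 5.3 does not, so the omission reads as a difference between visits. Section 5.3's different PK schedule shows that it cannot simply be read as a restatement of the chart.

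A reader might also infer that the own-control period is unmeasured for the secondary outcomes generally. The documents do not support that. Under section 5.3 only IgE is wholly missing; eosinophils, urinalysis, antibody serum and four PK samples remain, and one pre-drug IgE value exists on any reading. Nor is a drug profile lost on a day when no drug is given.

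A reader might further infer that the volume conflict undermines the vehicle control or distorts the CBC. Footnote f covers every infusion visit, so it does not single out the vehicle day, and the protocol gives no figure that links these volumes to a change in blood counts.

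**Conclusion.** The contradictions are in the current text and go beyond clerical detail, but their reach is limited. If sections 5.2 and 5.3 are followed as written, the before-and-after-vehicle IgE change is not measured in any subject, pre-drug IgE falls from four values to one, and vehicle-day PK falls from twelve points to four. On draw count, section 5.3 stands alone against three other places. The PK volume conflict is a separate matter affecting all infusion visits. With the draw count, it leaves total blood anywhere from roughly 450 to 588 mL per subject, on the assumption that the pre-dose PK draw and the time-0 sample are the same.

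The IgE conclusion assumes that staff work from the section 5 lists and not from the flow chart, which the protocol does not settle. No claim about precision is made: the planned summaries are descriptive, and how IgE change is defined and analysed can properly be left to the analysis plan. The point is worth correcting before the first infusion, because a vehicle-period IgE sample not assayed cannot be planned back in afterwards.

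**What to change.** Add IgE to the 22 mL test list in section 5.2 and to the one in section 5.3 (time 0 and 24 h), so that both match Appendix 1. Reconcile sections 3, 5.3, 5.4 and Appendix 1, with the synopsis, to one vehicle-day PK schedule and one PK sample volume. Say whether the separately listed pre-dose PK draw is the time-0 sample, so that the total blood volume follows from the text.

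The cost is wording, plus IgE assays on blood already being drawn: three per subject beyond the section 5 lists (Screening, Visit 1, Visit 1a), or 3 × 6 = 18 for the six volunteers, with one more for each screening failure tested. If the sponsor settles on twelve vehicle-day PK draws, that adds eight samples per subject relative to section 5.3; if on four, the synopsis, section 3 and Appendix 1 need the change instead.

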## Visits 2-2a, 3-3a and 4-4a (Treatment Visits, Day 8-9, Day 15-16, and Day 22-23), visit 2, 3 and 4 can be done ± 1 day from planned visit.

1. Baseline data will be collected at time 0 immediately prior to infusion of study medication and at 24h from initiation of infusion.
2. Body weight, vital sign (will be monitored during infusion) and physical examination.
3. Concomitant medications
4. Electrocardiogram (ECG) (will be performed only at time points 0 and 8 hr.)
5. Prepare drug for infusion (Section 6.5)

- Infuse 15units/kg (Visit 2)
- Infuse 30 units /kg (Visit 3)
- Infuse 60units/kg (Visit 4)

1. Concomitant medication use
2. Withdrawal of 22 mL venous blood for laboratory tests, pre infusion (time 0) and 24h post infusion which include:
3. Serum chemistries including electrolytes (K, Na, Cl, HCO3, Ca, and P), liver function tests (AST, ALT, LDH, AlkP, GGT, and Bilirubin), Renal function tests (BUN, and Creatinine,) CPK, Serum proteins(Albumin,Globulin), Cholesterol, and Uric Acid Complete blood cell count (CBC), and coagulation profile (PT, PTT)
4. ANF, ESR ,C3
5. Eosinophils, IgE
6. Urinalysis
7. Withdrawal 5ml PK blood for plasma sample prior to dosing
8. Administer the investigational drug (see Section 6.2) and monitor the same safety parameters as described in Visit 1
9. Withdrawal of 5ml blood for plasma samples at 0, 5, 45, 80 and 90 min during infusion and 100, 115, 130, 150, 180, 210 minutes and 24 hours post-infusion.
10. Withdrawal of 5ml blood for serum for antibody detection and characterization at 24h post infusion
11. Adverse events
12. Serum prGCD protein level will be checked at the end of the study for all subjects.
13. Anti human prGCD antibodies will be analyzed at the end of the study for all patients from blood serum samples taken 24hr post each infusion.

## Visit 5 (Follow-up Visit, Day 29) Visit 5 can be done ± 1 day from planned visit.

1. Adverse events
2. Concomitant medication use
3. Laboratory tests
4. Withdrawal of 22 mL venous blood for laboratory tests, which include:
   1. Serum chemistries including electrolytes (K, Na, Cl, HCO3, Ca, and P), liver function tests (AST, ALT, LDH, AlkP, GGT, and Bilirubin), Renal function tests (BUN, and Creatinine,) CPK, Serum proteins(Alb, Globulin), Cholesterol, and Uric Acid
   2. Complete blood cell count (CBC), and coagulation profile (PT, PTT)
   3. ANF, ESR, C3 (C3 test should be done both at time 0 and 24hr post infusion)
   4. Eosinophils, IgE
   5. Serum pregnancy test
5. Vital signs and physical examination including body weight.
6. Urinalysis
7. Withdrawal of 5ml blood for plasma for prGCD protein level detection
8. Withdrawal of 5ml blood for serum for antibody detection and characterization
9. Serum prGCD protein level will be checked at the end of the study for all subjects.
10. Anti human prGCD antibodies will be analyzed at the end of the study for all subjects.

## Observations and Measurements

### Blood Tests

Serum chemistries include electrolytes (K, Na, Cl, HCO3, Ca, and P), liver function tests (AST, ALT, LDH, AlkP, GGT, and Bilirubin), renal function tests (BUN, and Creatinine,) CPK, Serum proteins (Albumin and Globulin), Cholesterol, and Uric Acid.

Complete blood cell count (CBC), and coagulation profile (PT, PTT), ANF, ESR, C3, Eosinophils, and immunoglobulin including IgE.

